# Game-based health education to improve ART adherence of newly diagnosed young people with HIV: protocol for a stepped-wedge design randomized controlled trial

**DOI:** 10.1186/s12889-022-14708-2

**Published:** 2022-12-03

**Keywords:** Game-based education, Young people infected with HIV, Antiretroviral therapy, Adherence

## Abstract

**Background:**

Antiretroviral therapy (ART) is one of the most effective ways for HIV-infected to treat AIDS. However, it is difficult to start ART among young people those newly diagnosed HIV-infection in China, and their adherence to ART is poor. We have designed an AIDS educational game called AIDS Fighter · Health Defense, which could improve the AIDS-related knowledge and has the potential to improve AIDS prevention ability of young students. In this study, AIDS Fighter · Health Defense will be used with newly diagnosed young people with HIV to evaluate the education effect of the game in improving ART adherence.

**Design:**

A stepped-wedge design randomized controlled trial will be conducted to confirm the education effect of AIDS Fighter · Health Defense on improving ART adherence of newly diagnosed young people with HIV, and to verify when to start game-based health education could be more effective for newly diagnosed young people with HIV.

**Methods:**

Participants will receive AIDS education from health workers and start ART when diagnosed with HIV and assigned into four groups randomly. The first step group to the fourth step group will receive AIDS Fighter · Health Defense in turn at the star of ART, one week, one month and three months after the start of ART. The primary outcomes are medication adherence, CD4( +) T cell count, and HIV viral load. The secondary outcomes are ART-related knowledge, ART-related skills, psychological resilience, and self-discrimination. Assessments will be completed before the intervention and one week, first month, and third month of the intervention, and then a one-year follow-up evaluation will be conducted after the intervention.

**Discussion:**

AIDS Fighter · Health Defense may be an effective approach to help newly diagnosed young people with HIV to improve ART adherence. A stepped-wedge design randomized controlled trial of this study may find the optimal time of AIDS education to improve ART adherence of newly diagnosed young people with HIV.

**Registration number:**

Chinese Clinical Trial Registry: ChiCTR2200059766, registered 11 May 2022. http://www.chictr.org.cn/showproj.aspx?proj=169420

**Supplementary information:**

The online version contains supplementary material available at 10.1186/s12889-022-14708-2.

## Background

Antiretroviral therapy (ART) is one of the most effective treatments for HIV-infected [1]. There is a global consensus that adherence to ART is critical to the success of HIV treatment [2, 3]. Good ART adherence of HIV-infected could help them maintain viral suppression [4], reduce HIV contagiousness [5], maintain high CD4( +) T cell count and reduce the incidence of AIDS-related complications [6]. In China, 92.6% of people live with HIV (PLHIV) had access to ART by the end of 2021 [7]; And a study of 1198 PLWH from Guangxi, China, showed 80.3% of people receiving ART had optimal medication adherence [8]. While some progress has been made in ending the AIDS epidemic, another point of concern should be noted, namely the persistence of ART adherence [9]. A meta-analysis of ART adherence in China showed that, the mean ART adherence among HIV-infected in China was 81.1% at one week of ART initiation, 80.9% at one month of ART initiation, and dropped to 68.3% at three months of ART initiation [10]. Which means that a sharp decline occurred within three months, making it more difficult to adhere to long-term antiviral treatment.

Adolescents have lower adherence rates than children and adults [11–13]. According to a Ugandan study, only 63.4% of young people are adhered to their ART consistently [14]. In 2021, there are over 1.14 million cases of HIV infection, of which young people aged 15–25 account for about 36% [15, 16]. Even among those newly infected, approximately 28% are young people [17]. Moreover, it is difficult for newly diagnosed young people with HIV to start ART. A survey showed that only 39.5% of young people infected with HIV could initiate ART in a timely manner [18], and ART adherence was poor after initiation [19]. Lack of ART related knowledge is one of the important reasons affecting the medication behavior of young people [20]. AIDS health education has been shown to be an effective way to improve the self-management ability of young people infected with HIV [21]. However, there is a lack of health education on ART adherence among newly diagnosed young people with HIV [22].

Game-based health education has been widely used in disease education, like diabetes [23], breast cancer [24], cardiovascular disease [25], etc., and has been shown to have good educational effects. Game-based health education on AIDS was mainly aimed at young people [26], including HIV-infected adolescents, gay men, and other high-risk groups [27, 28]. The goals of education were to increase the adherence with pre-exposure prophylaxis (PrEP) and ART [29, 30], promote AIDS screening [31], reduce risky sexual behaviors and avoid drug and alcohol abuse [32–34]. However, there were few studies on game-based health education on ART in newly diagnosed young people with HIV.

We have developed an AIDS educational game called AIDS Fighter· Health Defense, which has seven levels with difficulty increasing as the levels continue. The storyline of the game is that HIV has invaded the human body, and players need to fight to clear HIV. Players are required to collect ART medicine and condoms, avoid HIV, alcohol and drug, take ART medicine regularly, and answer questions about ART. More information about the game can be found in our published studies [35, 36]. It had been shown that the game can improve the AIDS-related knowledge and has the potential to improve AIDS prevention ability of young students. Therefore, we believe that AIDS Fighter· Health Defense could be an effective, large-scale intervention tool for AIDS health education. In this study, AIDS Fighter · Health Defense will be used with newly diagnosed young people with HIV to evaluate the education effect of the game in improving ART adherence.

Below we describe the protocol of our stepped-wedge design randomized controlled trial to evaluate the effect of the game to improve the ART adherence of newly diagnosed young people with HIV. The trial is a 3-month game-based intervention, and the game includes components designed to increase ART adherence, ART knowledge, ART skills, psychological resilience and perceived benefits, and to reduce self-discrimination, anxiety and depression.

## Methods/Design

### Study design

A stepped-wedge design randomized controlled trial with four groups will be conducted. Which is a relatively new research design [37]. The design included an initial phase in which no groups are exposed to the intervention. Subsequently, at fixed time intervals (“steps”), a group (or set of groups) is randomly crossed over from the control to the intervention under evaluation. The start of the intervention is different for each group, and this design helps to verify the effect of intervention timing on intervention effect.

Participants will be assigned to the four groups in 1:1:1:1 randomly. There is no dedicated control group in this study, and each step group will receive AIDS Fighter · Health Defense intervention in turn as the trial progress (see Fig. 1 for study workflow diagram). The group which has not received the intervention will be treated as the control group. Data collection will be conducted before and after intervention in each group. Participants in each group will be evaluated for medication adherence after the first week of intervention and the other outcomes will be evaluated after the first month and third month of intervention. Follow-up evaluations for the same outcomes will be performed at 6 and 12 months after the end of the intervention.

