### Intervention design

Participants will receive AIDS education from health workers and start ART when diagnosed of HIV and randomly assigned into four groups. The first step group to the fourth step group will receive AIDS Fighter. Health Defense in turn at the start of ART, one week after the star of ART, one month after the star of ART and three months after the star of ART. Assessments will be completed before the intervention and after the first week, first month, and third month of intervention, and then a one-year follow-up evaluation will be conducted. The intervention design is shown in Fig. 2.

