### The first step intervention group

The first step group will receive the intervention of the educational game “AIDS Fighter · Health Defense” through WeChat at the time of enrollment and will be required to play the game at least 5 days a week and 20 min a day. During the 3-month intervention, participants will receive daily message notifications that inform users to play the game. A data management system will be used to monitor participants' time in the game and check details of the participant's use of the game.

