### The 2-4 step intervention group

The intervention of 2-4 step groups will be same as the first step intervention group, but the time they receive AIDS Fighter · Health Defense will be different. The second step group will receive the intervention 1 week after starting ART. The third step group will receive the intervention 1 month after starting ART. The fourth step group will receive the intervention 3 months after starting ART.

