### Randomization and allocation concealment

Opaque envelopes will be used for randomization. Among the 700 envelopes, each envelope contained a note with the words "First Step Group", "Second Step Group", "Third Step Group" and "Fourth Step Group" (175 envelopes per group). An opaque envelope will be selected for the first time the participant enrolled, and they will be assigned to the corresponding group according to the envelope. The health workers for the AIDS education of newly diagnosed young people with HIV and the data analysts will be blinded for the allocation.

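### Everyone is randomised at enrolment, but the text times every assessment from each group's own game start, so loss to care during the wait can select the analysed set differently by group

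*Protocol article*

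**What the plan says.** All references are to the protocol article.

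- **Allocation.** Study design: "Participants will be assigned to the four groups in 1:1:1:1 randomly". Randomization and allocation concealment: "An opaque envelope will be selected for the first time the participant enrolled". Allocation is individual and takes place at enrolment.
- **Assessments.** Study design: "Data collection will be conducted before and after intervention in each group". Intervention design: "Assessments will be completed before the intervention and after the first week, first month, and third month of intervention". The Abstract gives the same timing. The later follow-ups fall 6 and 12 months after the intervention ends, so they too run on each group's own clock.
- **Game start.** The first step group gets the game "through WeChat at the time of enrollment" according to its own section, but at the start of ART according to Intervention design. For the longest wait: "The fourth step group will receive the intervention 3 months after starting ART". Steps 2 and 3 wait 1 week and 1 month.
- **Control data.** Study design uses any group still waiting for the game as the control. The sample size section assumes seven observation periods and a 20% loss, the same in every group.

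Figures 1 and 2, which are said to show the workflow and the intervention design, could not be seen for this review.

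**The concern.** In steps 2 to 4 the first stated assessment comes after randomisation, by up to 3 months of ART. Anyone who leaves care in that interval is randomised but has no scheduled outcome visit. In step 1 the first assessment coincides with the start of follow-up, so a similar person supplies at least early data before leaving. Membership of the analysed set is then partly decided after randomisation, and by an amount that depends on the allocated group.

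Two of the three hypotheses are exposed. The first compares people who have the game with people still waiting for it, and the waiting groups' data come only from those who stayed to the end of the wait. The second compares start times, so it sets groups with different amounts of unseen early loss against each other. The Background puts the main fall in adherence inside step 4's wait: 80.9% at one month of ART and 68.3% at three.

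The planned GEE and mixed models use whatever outcomes a person has. They can use a step 1 leaver's early values. They cannot use a step 4 leaver who has none. So the two groups' leavers may be handled differently without anyone having chosen such a rule.

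**Working it through.** **1. The schedule as the text gives it.** Times are counted from ART start. Step 1 is placed at time 0, as Intervention design does. The game lasts 3 months, so the follow-ups fall 3 + 6 = 9 and 3 + 12 = 15 months after game start.

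| Group | First assessment (game start) | During the game | Follow-up |
|---|---|---|---|
| Step 1 | 0 | 1 wk, 1 mo, 3 mo | 9, 15 mo |
| Step 2 | 1 wk | 2 wk, 1 mo + 1 wk, 3 mo + 1 wk | 9 mo + 1 wk, 15 mo + 1 wk |
| Step 3 | 1 mo | 1 mo + 1 wk, 2 mo, 4 mo | 10, 16 mo |
| Step 4 | 3 mo | 3 mo + 1 wk, 4 mo, 6 mo | 12, 18 mo |

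Three things follow.

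- Each group has six occasions (one before, three during, two after). The sample size section counts seven periods and does not date them.
- Each waiting group gives one untreated observation, at the end of its wait. At 1 week of ART, steps 3 and 4 are both untreated and neither is scheduled. At 1 month, step 4 is untreated and not scheduled. A group meant to serve as control while it waits needs those observations.
- A person lost in month 2 has already passed three occasions in step 1 (before, 1 week, 1 month). In step 4 the same person has passed none of the six.

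**2. The plan's own figures.**

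- Planned effect: 95% − 81.1% = 13.9 points.
- Loss allowance: 140 / (1 − 0.20) = 175 per group, and 4 × 175 = 700. Both reproduce. The allowance restores numbers, not comparability.

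**3. Illustration of size.** The inputs are:

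- p = 68.3% adherence at three months of ART (Background), taken as true for everyone randomised to step 4;
- L = share of step 4 lost during the wait. The article gives no such figure, so a range of 5% to 20% is assumed;
- all leavers are non-adherent, also an assumption.

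Observed adherence among attenders = p / (1 − L), with 0.683 × 175 = 119.5 adherent people.

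| L | Attenders | Observed | Above 68.3% |
|---|---|---|---|
| 5% | 166.25 | 119.5 / 166.25 = 71.9% | 3.6 points |
| 10% | 157.5 | 119.5 / 157.5 = 75.9% | 7.6 points |
| 20% | 140 | 119.5 / 140 = 85.4% | 17.1 points |

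The excess would equal the planned 13.9 points at L = 1 − 0.683 / 0.822 = 16.9%.

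**4. When this becomes a between-group bias.** Suppose the game has no effect and L = 10% in both groups.

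- If leavers are missing from the 3-month comparison in both groups, step 1 also shows 0.683 / 0.90 = 75.9%, and the difference is 0.
- If step 1 leavers count as non-adherent and step 4 leavers are missing, the figures are 68.3% and 75.9%, and the difference is 7.6 points.

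The numbers in step 3 are therefore the far end of a range that starts at zero.

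**The case against.** **The text may not be the whole schedule.** Using waiting groups as the control, describing an initial phase with no group exposed, and counting seven observation periods all imply some measurement during the wait. The assessment times (1 week, 1 month, 3 months) also match the start times of steps 2 to 4, which would suit a common clock, and the figures may show one. This stands as a limit: the absence of waiting visits is a reading of the text, not something it states. But the sentences that do time assessments tie them to each group's own intervention, so text and design conflict and need reconciling either way.

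**Adherence may not depend on the visit.** MPR rests on days covered by doses. If it comes from dispensing records, it can be obtained for the wait without a game visit. That stands for MPR. It does not help CD4 count, viral load, the recall questionnaire or the secondary scales.

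**Never-starters.** The Background reports that "only 39.5% of young people infected with HIV could initiate ART in a timely manner", and eligibility asks only for a recent diagnosis. A reader might infer that large numbers in steps 2 to 4 never reach a first visit while the same people in step 1 are fully assessed. The article does not support that. Intervention design has everyone start ART at diagnosis. It also ties step 1 to ART start, so a never-starter might not reach the game there either. MPR divides by days on ART, so it is undefined for never-starters in any group. The 39.5% figure concerns timely start in an outside survey, and a late starter still gets a first visit.

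**Analysis rules.** How leavers are scored, and any sensitivity analysis for missing data, can properly sit in a statistical analysis plan. That is accepted. But no analysis plan can supply visits that were never scheduled.

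**Conclusion.** The point holds as a fault in the stated assessment schedule. Randomisation is at enrolment, and as written steps 2 to 4 have no assessment before it or during the wait. Selection into the analysed set after randomisation can therefore differ by group and bias hypotheses 1 and 2. The same schedule conflicts with the waiting groups' role as control and with the seven observation periods.

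The size of any bias cannot be derived from the article. The 3.6, 7.6 and 17.1 points rest on an assumed loss during the wait, on every leaver being non-adherent, and on 68.3% holding for all randomised. They count as a difference between groups only to the extent that step 1 leavers are handled differently. A reader might infer that randomisation is already broken, or that later-start groups are sure to look better. Neither is established: the figures are unseen, and like handling of leavers in both groups could remove the difference.

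It should be corrected before enrolment, because a missed assessment before randomisation cannot be recovered later.

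**What to change.** 1. Assess every participant at enrolment, before the envelope is opened: CD4 count, viral load and the questionnaires. Adherence does not yet apply.
2. Place assessments in all four groups at common times from enrolment or ART start, so that waiting groups supply control data while they wait. State the dates of the observation periods and make them agree with the count in the sample size section.
3. Keep all 700 randomised participants in the analysis. Obtain MPR over the wait from dispensing records whether or not the game visit took place.
4. Reconcile the two statements of when step 1 begins (at enrolment, or at the start of ART), and check the text against Figures 1 and 2.

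**Cost.** This is a protocol amendment. The baseline assessment moves earlier for 3 × 175 = 525 people, using measures already in the plan. Common times may add contacts during the wait: for example, if the 1-week and 1-month times are used, one at 1 week for step 3 and two, at 1 week and 1 month, for step 4. Adherence figures may look less favourable, because early failures would be seen.

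### Visits are timed from each group's own game start, so comparing the step groups at the same visit label mixes start time with time on ART (hypothesis 2)

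*Protocol article*

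**What the plan says.** The protocol article states the visit clock in the Abstract, in Study design and in Intervention design, each time relative to the game.

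- Intervention design: "Assessments will be completed before the intervention and after the first week, first month, and third month of intervention".
- Study design, adherence: "Participants in each group will be evaluated for medication adherence after the first week of intervention".
- Study design, remaining outcomes: "the other outcomes will be evaluated after the first month and third month of intervention".
- Study design, long term: "Follow-up evaluations for the same outcomes will be performed at 6 and 12 months after the end of the intervention".

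The game lasts the same time in every group: "The trial is a 3-month game-based intervention" (Background). Its start is staggered. Step 1 receives it "at the time of enrollment and will be required to play the game" (The first step intervention group), which Intervention design equates with the start of ART. Steps 2 and 3 follow at 1 week and 1 month, and "The fourth step group will receive the intervention 3 months after starting ART" (The 2-4 step intervention group).

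Hypothesis 2 is that the time of game start affects adherence. The Abstract and the Discussion present finding the best start time as a main aim. The Background says that mean adherence in China was 81.1% at one week of ART and 80.9% at one month, and "dropped to 68.3% at three months of ART initiation". The text gives no assessment calendar in ART time that all groups share.

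**The concern.** A start-time comparison asks whether otherwise similar people do better when the game begins earlier or later. Randomisation makes the groups alike at the start of ART. Comparing them at the same visit label then sets people early in ART against people up to three months further on. Adherence declines over exactly that stretch, according to the protocol's own Background. CD4 count and viral load can also be expected to change with time on treatment.

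An apparent advantage of early start could therefore be nothing more than step 1 being measured before the usual decline and step 4 after it. Questionnaire, CD4 and viral-load values that are not collected at common ART times cannot be recovered later, so the calendar has to be settled in the protocol.

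**Working it through.** **Inputs**

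- Game-start delay (Intervention design and the step-group sections): 0, 1 week (about 0.23 month), 1 month, 3 months.
- Visits after game start: 0 (pre-game), 1 week, 1 month, 3 months. Follow-up is 6 and 12 months after a 3-month game, so 3 + 6 = 9 and 3 + 12 = 15 months after game start.
- Adherence by ART time (Background): 81.1%, 80.9% and 68.3% at 1 week, 1 month and 3 months.
- Sample size calculation: 81.1% raised to 95%, a planned effect of 95 − 81.1 = 13.9 points; 140 per group before loss. The inflation reproduces: 140 / 0.8 = 175, and 4 × 175 = 700. I take the 140 as stated. How it was derived is a separate matter and does not bear on the calendar.

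**Step 1: place the visits on the ART clock.** ART time = delay + time since game start, in months:

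| Group | Pre-game | 1 wk | 1 mo | 3 mo | +6 mo | +12 mo |
|---|---|---|---|---|---|---|
| Step 1 | 0 | 0.23 | 1 | 3 | 9 | 15 |
| Step 2 | 0.23 | 0.46 | 1.23 | 3.23 | 9.23 | 15.23 |
| Step 3 | 1 | 1.23 | 2 | 4 | 10 | 16 |
| Step 4 | 3 | 3.23 | 4 | 6 | 12 | 18 |

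In every column step 4 is 3 months ahead of step 1. Steps 1 and 2 differ by only 7 days.

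**Step 2: can a model separate the effects?** After game start, ART time is exactly delay plus exposure time. A design matrix with an intercept and these three linear terms has rank 3 of 4, so the linear effects cannot all be estimated.

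**Step 3: size under a null game.** Assume no game effect and no timing effect, read the Background means as proportions (as the sample size section does), interpolate linearly between them, and hold 68.3% after month 3.

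- First-week visit: 81.1%, 81.0%, 79.4% and 68.3% in steps 1 to 4. Step 1 minus step 4 is 81.1 − 68.3 = 12.8 points.
- Pooled two-sided 5% test of step 1 versus step 4, 140 per group: mean proportion 0.747. The null SE is √(2 × 0.747 × 0.253 / 140) = 0.0520. The SE under the difference is √((0.811 × 0.189 + 0.683 × 0.317) / 140) = 0.0514. Then (0.128 − 1.96 × 0.0520) / 0.0514 ≈ 0.51, a rejection probability of about 0.69.
- First-month visit: 80.9 − 68.3 = 12.6 points, rejection about 0.68.
- Third-month visit: 68.3% in all groups, so no artefact.
- A four-group chi-square test would reject about 72% of the time at the first-week visit and 62% at the first-month visit.

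**Step 4: vary the assumption.** The decline from month 1 to month 3 is (80.9 − 68.3) / 2 = 6.3 points per month. If it continued to month 6, the step 1 versus step 4 gaps would be 14.3, 18.9 and 18.9 points at the first-week, first-month and third-month visits, with rejection about 0.78, 0.94 and 0.90. If only half the 12.8-point gap arose (81.1% versus 74.7%), rejection at the first-week visit would be about 0.25.

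**Step 5: hypothesis 1.** In the table, the pre-game visits of steps 2, 3 and 4 (ART 0.23, 1 and 3 months) coincide with step 1's visits at 1 week, 1 month and 3 months. If they are held just before the game begins, they give exposed versus unexposed contrasts of 175 versus 175 at equal ART time. A calendar common to all groups would allow 175 versus 525, 350 versus 350 and 525 versus 175. Compared with 1/175 + 1/175, the variance falls by these factors:

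- Week 1 and month 3: (2/175) / (1/175 + 1/525) = 1.5.
- Month 1: (2/175) / (2/350) = 2.0.

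**The case against.** **The calendar may be in the figures.** Figs. 1 and 2 are not available here. The step times use the same grid as the visits, treating not-yet-exposed groups as controls suggests parallel measurement, and the sample size section counts 7 observation periods where the own-start clock yields six visits. A common calendar may be intended. The text nevertheless states the own-start clock three times and a common one nowhere, so the point stands as one about what is written.

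**The planned models handle time.** Data analysis names generalised estimating equations, mixed models and a difference-in-difference meant to remove change over time. This does not rescue the start-time contrast. No group is unexposed after ART month 3, and step 4 has no stated visit at ART week 1 or month 1. Step 1's pre-game visit is at ART day 0, where a possession ratio divided by days on ART is undefined.

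**A reader might infer that the game-versus-control effect is confounded too.** The documents do not support that. Step 5 of the working gives contrasts at equal ART time, so the loss there is mainly efficiency. Study design, read literally, offers fewer of them: it ties adherence to the first week and the other outcomes to months 1 and 3, whereas Intervention design lists all three visits without that split.

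**A reader might infer that waiting time goes unmeasured and that step 4 is a selected sample.** The text does not establish either. The possession ratio covers all days on ART, so step 4's pre-game value spans its waiting period. An enrolment assessment or later retrieval of data is not ruled out.

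**No clock separates the three time scales.** This is correct. The own-start clock holds exposure time equal, and the ART clock holds ART duration equal. What favours the ART clock is that it compares randomised groups at the same time since a common origin. The choice should be stated as a choice of estimand.

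**Conclusion.** The point holds for hypothesis 2 and the search for the best start time. As written, groups at the same visit label differ by up to three months on ART, and the protocol's own figures say adherence changes over that span. Under a null game the early-visit artefact is 12.8 points, close to the 13.9 points the trial is planned to detect.

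The 69% should not be read as the trial's false-positive rate. It describes one unadjusted comparison of the two most distant groups at one early visit. It also rests on reading mean adherence as a proportion, on meta-analysis means for people with HIV in China in general rather than for this age group, and on a flat 68.3% after month 3. Under that last assumption the artefact disappears at the third-month visit; if the decline continues, it does not. Hypothesis 1 is not inherently confounded.

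**What to change.** 1. Define the assessment calendar in time since ART start, common to all four groups: enrolment, 1 week, 1 month, 3 months, 6 months, then common later dates. Reconcile it with Figs. 1 and 2 and with the stated 7 observation periods.
2. Analyse by randomised group, with ART time as a categorical fixed effect and an exposed/not-yet-exposed term. Concurrent unexposed data for that term end at ART month 3.
3. Compare start times at common times since ART start, ideally at a late date after all groups have finished the game (step 4 finishes at 3 + 3 = 6 months).
4. State that groups at equal ART time differ in exposure or in time since the game ended. At ART month 3, step 1 has had 3 months of game and step 4 none. At ART month 12, step 1 finished 9 months earlier and step 4 finished 6 months earlier.
5. Where added visits are not feasible, at least compute the possession ratio at common ART times and fit ART time in the models.

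The cost is an amended visit calendar and a few added questionnaire and laboratory assessments in the waiting groups. Step 1's visits up to month 3 already fall on the new grid.
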